### Intervention condition - judging and co-creation group

Along with the crowdsourced interventions, participants in the intervention condition will be additionally engaged by a series of judging on materials co-created by a small group of participants. This small co-creation group will be selected from trial participants based on their willingness to contribute and areas of expertise while also considering their self-identified gender and sexual identity. The co-creation group will generate materials regularly to address adhering to PrEP. Co-creations that are only tailored to the experience of one population will be tweaked by the study group before sending to other populations in the sample to better reflect the latter’s specific experience. The co-created materials will be sent to all participants in the intervention condition for judging. The judging criteria will include 1) potential to encourage PrEP adherence; 2) creativity; 3) potential to engage social media users; 4) feasibility for real-world implementation. Materials that have the highest scores will be shared publicly on social media platforms.

### Control condition

When clusters are not in the intervention condition, they will be in the control condition. Control condition includes a baseline program using WeChat mini-app to promote sexual and mental health awareness and routine follow-ups by CBOs and hospitals. This mini-app promoting sexual and mental health awareness among Chinese gender and sexual minorities is predesigned by the research team and will be directly accessed on WeChat mini-app store for free [25]. The mini-app comprises synthesized LGBTQ-friendly information on PrEP (what is PrEP, benefits of PrEP, who can use PrEP, how to use PrEP, etc.) and other sexual and mental health-related content, and allows participants to apply for free HIV self-tests and communicate with study staff members directly. Participants will be introduced to the mini-app at baseline recruitment and will be encouraged to use the mini-app throughout the study. Participants will also receive follow-ups from the hospitals and CBOs at 3-month intervals to assess PrEP uptake and adherence. The follow-ups include an online follow-up survey to track PrEP adherence and a clinical assessment for ongoing PrEP uptake. The follow-up survey will be administered by CBO peer educators or volunteers, who will be responsible for sending out the survey and collecting survey responses. The clinical assessment will be performed by experienced physicians in the hospitals following standard guidelines.

### Study measures and outcomes

A baseline survey will collect data related to sociodemographic characteristics, sexual behaviors, experiences and perceptions of PrEP, sociopsychological assessments related to PrEP use, and co-creation willingness. Sociodemographic characteristics include participants’ age, gender identity, sexual orientation, socioeconomic status, medical insurance status, and housing. Sexual behaviors variables include number of sexual partners, casual sex in the past 6 months, sex work in the past 6 months, sex under the influence of substance (including stimulants or poppers, alcohol, cocaine or speed/crystal meth) in the past 6 months, HIV testing, STI testing, and self-assessed HIV infection risks. Experiences and perceptions of PrEP include awareness, willingness, preferences, previous use of PrEP, PrEP attitudes, PrEP stigma, and PrEP use self-efficacy. Sociopsychological assessments include HIV-related anxiety, social support, and overall perceived stress. Co-creation willingness asks whether the participant would be willing to join a co-creation group, and their areas of expertise if they agree to. Participation in the PrEP open call will also be captured. For self-identified transgender individuals, data related to gender-affirming interventions, lifetime involvement in sex work, and community connectedness will also be collected. Baseline and follow-up surveys will be built online using Sojump (Sojump, Shanghai, China).

Each follow-up at the 3, 6, 9, 12 months will include an online survey and a clinical assessment. (Table 1) The online survey will collect data related to number of sexual partners, HIV testing, PrEP uptake (missing doses in the past 90, 30, 7 days for daily PrEP users vs. number of sex and number of doses taken in the past 90, 30 days for on-demand PrEP users), engaging in WeChat mini-app, and evaluation of crowdsourced PrEP adherence intervention. Participants will be assessed on their PrEP attitudes, PrEP stigma, PrEP use self-efficacy, HIV-related anxiety, social support and overall perceived stress using validated scales at 6 and 12 months. For all follow-ups, transgender participants will additionally respond to questions related to whether they are currently using gender affirming hormones, and if they were, whether they are concerned about drug-drug interaction and whether they have mentioned taking hormones to the doctors who are prescribing PrEP. The clinical assessment will include testing results related to HIV, STIs (syphilis, HBV, HCV), standard blood test, standard urine test, liver function test, and renal function test. If a participant seroconverts to HIV positive, their participation in the study will be terminated and they will be referred to their local provider or health department for antiretroviral therapy. Otherwise, participants will be prescribed TDF-FTC for another 3 months after each follow-up at 3, 6, 9 months.

The primary outcomes of this sub-study are PrEP adherence and retention in PrEP care throughout the study period. PrEP adherence will be measured by self-report in quarterly behavioral assessment surveys and pill count at clinical follow-ups among a subset (a total of 120 participants who initiate PrEP during the study in Guangdong will be sampled to receive pill count using systematic random sampling). Retention in PrEP care will be measured via self-initiated or physician-advised PrEP discontinuation, PrEP re-initiation, and self-initiated switch rates from once daily and on-demand regimens. Details about the study measures are illustrated in Table 2. Optimal daily PrEP adherence will be considered to be 6–7 pills weekly. Optimal adherence to an on-demand regimen will be defined as having two pills at least 2 h before each sexual encounter, followed by one pill 24 hours after the first dose and one pill after the second dose.

**Table 2 Tab2:** Outcome measures and timepoints of data collection

Outcomes	Measure	Data collection timepoints
**Primary outcomes**		
**Retention in PrEP care**	Number of participants completed clinical follow-ups	3, 6, 9, 12 months
**PrEP adherence**	1. Self-report in follow-up surveys: During the past 7 days and 30 days: (1) self-report taking once daily regimen: number of missed pills; perceptions of whether they had taken < 60%, 60–90%, or > 90% doses. (2) self-report taking on-demand regimen: number of sex events that are not covered by any PrEP (0 pills taken); correctly covered by PrEP (2 pills on the sex day (X) and X + 1, X + 2; or at least one pill taken on days X, X + 1, and X + 2 if the days between two sex events are less than one week); partially covered by PrEP (any other use). 2. Pill count at clinical visits: number of unused pills counted at each clinical follow-up (in-person or via phone) 3. Medical possession ratio: [(total days between first fill and end of follow-up) – (number of days without TDF-FTC in possession)] / total days of follow-up, based on medical refilling records	3, 6, 9, 12 months
**PrEP discontinuation**	120 days without TDF-FTC in possession based on medical refilling records.	3, 6, 9, 12 months
**PrEP reinitiation**	Number of participants who discontinued TDF-FTC according to the study definition and then successfully restart PrEP, based on self-report and medical refilling records.	3, 6, 9, 12 months

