### Intervention condition - receiving the intervention materials

Participants will be assigned into four clusters in blocks at each site. All clusters will receive the intervention initiated at a different time. Updated interventions 2.0, 3.0, 4.0 will be implemented for clusters b, c, d, respectively, in addition to cluster a receiving intervention 1.0. Each cluster will receive the intervention for 3 months over a 12-month period. The first intervention will start 2 weeks after the baseline recruitment. The time intervals of the crowdsourced intervention are aligned with the follow-up intervals in the PrEP Demo study. That is, the first cluster will receive their first intervention 2 weeks after they fill out the baseline survey, and the second, third, and fourth cluster will receive their first intervention 2 weeks after they complete the follow-up surveys at 3, 6, 9 months respectively. The intervention will be delivered to each cluster biweekly in the 3-month intervention period by the CBOs. CBO peer educators or volunteers will contact participants via WeChat and implement the intervention each time.

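### The 120-day discontinuation rule, the re-initiation count that depends on it and the cumulative possession ratio do not fit exposure windows of about 77 to 91 days, so these refill-based primary measures cannot separate intervention from control time

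*Protocol article*

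**What the plan says.** In the protocol article, Table 2 (Primary outcomes) defines three measures from refill records and schedules all of them at 3, 6, 9 and 12 months:

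- Discontinuation: "120 days without TDF-FTC in possession based on medical refilling records".
- Re-initiation: "Number of participants who discontinued TDF-FTC according to the study definition and then successfully restart PrEP".
- Possession ratio, the third of three adherence measures. Its numerator starts from "total days between first fill and end of follow-up", less the days without drug, and is divided by total follow-up. It is therefore cumulative.

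The text under Study measures and outcomes also names discontinuation and re-initiation as ways of measuring retention, one of the two primary outcomes. On supply, the same section says "participants will be prescribed TDF-FTC for another 3 months after each follow-up at 3, 6, 9 months". The size of the first supply is not given.

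On exposure, the section on receiving the intervention materials says "Each cluster will receive the intervention for 3 months over a 12-month period". For timing, "the first cluster will receive their first intervention 2 weeks after they fill out the baseline survey", and the later clusters follow the same pattern: the "fourth cluster will receive their first intervention 2 weeks after they complete the follow-up surveys at 3, 6, 9 months respectively". The Control condition section treats a cluster as control whenever it is not in its intervention period. The Analysis section specifies a generalized linear mixed model with intervention status and time as fixed effects.

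**The concern.** In this design the effect is estimated by comparing cluster-periods under intervention with cluster-periods under control. An outcome can serve that comparison only if what is recorded at a visit reflects behaviour in the period ending at that visit. A 120-day gap is longer than a three-month step, and the clock starts only when the supply runs out, so an event is recorded well after the behaviour that caused it, often under the other condition. A ratio accumulated from first fill carries all earlier control time into each later value. If these measures are used as defined, events are credited to the wrong condition and any effect on refilling is blurred or missed.

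**Working it through.** The plan gives no derived figure that rests on these definitions, and its sample size calculation does not bear on the point. The check is day arithmetic.

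**Inputs.** Visits at months 3, 6, 9 and 12, taken as days 91, 183, 274 and 365. Intervention starts 14 days after baseline (cluster a) or after the surveys at months 3, 6 and 9 (b, c, d). Gap length is 120 days. Follow-up ends at day 365. The first supply is not stated, so 0 to 90 days is assumed as a range.

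**Step 1: earliest possible discontinuation.** Earliest day = first supply + 120.

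- 0 days: 120
- 30 days: 150
- 60 days: 180
- 90 days: 210

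All exceed 91, so the outcome is zero by definition at month 3, which is the visit closing cluster a's window. Against day 183, it is also zero at month 6 with a 90-day first supply, but not with 0, 30 or 60 days.

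**Step 2: onset of a gap that is complete when the window closes.** Latest onset = closing visit − 120.

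| Cluster | Start (day) | Closing visit (day) | Exposed days | Latest onset (day) |
|---|---|---|---|---|
| a | 0 + 14 = 14 | 91 | 77 | 91 − 120 = −29 |
| b | 91 + 14 = 105 | 183 | 78 | 183 − 120 = 63 |
| c | 183 + 14 = 197 | 274 | 77 | 274 − 120 = 154 |
| d | 274 + 14 = 288 | 365 | 77 | 365 − 120 = 245 |

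Every latest onset precedes the start of intervention. Running each window for a full three months (91 days) changes nothing, since 91 < 120.

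**Step 3: where gaps that begin under intervention are counted.** Completion = onset + 120.

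- a: onset days 14–91, complete days 134–211, counted at month 6 or 9, when a is back in control.
- b: onset days 105–183, complete days 225–303, counted at month 9 or 12, again in control.
- c: onset days 197–274, complete days 317–394. Only those begun by day 245 are counted, at month 12.
- d: earliest completion 288 + 120 = 408, after day 365. None is counted.

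Re-initiation requires a completed gap first, so it is later still.

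**Step 4: supply.** For a participant whose previous supply ends at the visit, a missed refill is flagged at:

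- due month 3: 91 + 120 = 211 (counted at month 9)
- due month 6: 183 + 120 = 303 (counted at month 12)
- due month 9: 274 + 120 = 394 (never counted)

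In b, c and d the three-month supply is prescribed about 2 weeks before exposure starts, so possession within the window is largely set beforehand. The refill that the intervention can influence is the next one. For c that is the month-9 refill, whose omission the 120-day rule never records. For d no later refill is planned within follow-up.

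**Step 5: possession ratio.** Share of the cumulative denominator that is intervention time:

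- At the closing visit: 77/91 = 85% (a), 78/183 = 43% (b), 77/274 = 28% (c), 77/365 = 21% (d).
- At month 12: 77/365 or 78/365, about 21% in every cluster. With a full 91 days it would be 91/365 = 25% in a to c, and still 21% in d.

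On the first count, a participant with no drug throughout the window and full possession otherwise still has a 12-month ratio of 1 − 77/365 = 0.79.

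**The case against.** The strongest reply is that the Analysis section describes a binary primary outcome evaluated at the end line, with adherence as the hypothesis. It does not say that discontinuation or the possession ratio enters the mixed model period by period, and that mapping may sit in an analysis plan that is not shown. This stands as a limit: the misattribution follows if the stated definitions are used to compare conditions. It does not remove the point, because the definitions and their quarterly schedule are fixed in Table 2. End-line use does not help either, since by month 12 all clusters have had about the same amount of exposure.

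A second reply is that a stepped wedge usually keeps clusters exposed after crossover. Clusters a, b and c would then have 351, 260 and 168 exposed days, enough for a 120-day gap. But the article states three months and then control. Even with sustained exposure, month 3 stays at zero and cluster d still has only 77 days.

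Three stronger readings are tempting and not supported:

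- A reader might infer that discontinuation cannot be observed in cluster d at all. It can. Gaps begun under control, by day 245, are countable there. What cannot be counted is a gap beginning under intervention.
- A reader might infer that discontinuation is zero at month 6 as well. That holds only if the first supply is about 90 days. The article does not state it, and the clinical visits at months 1 and 2 make shorter fills plausible.
- A reader might infer that the trial cannot answer its question. Self-reported adherence uses 7- and 30-day recall, pill count is taken at each clinical follow-up, and the Table 2 retention row counts completed visits. All of these fit the quarterly step.

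It is also fair to say that the possession fault lies in the measure as defined and not in the data, since interval values can be derived from the same refill records.

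**Conclusion.** The point holds for the refill-based primary measures and only for them. Discontinuation is zero by definition at month 3 whatever the first supply. In all four clusters, any gap complete at the visit closing the window began under control. In cluster d, no gap beginning under intervention can be counted. Re-initiation inherits this. The possession ratio mixes conditions at every visit, and about 21% of its month-12 denominator is intervention time. That figure is a share of time, not an estimate of bias: the article gives no possession rates from which a bias could be computed.

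The conclusion rests on the stated three-month exposure followed by control, visits close to schedule, and follow-up ending at 12 months. Only the month-6 result depends on the unstated first supply. The definitions should be corrected before analysis. The self-report, pill-count and visit-completion measures need no change on this account.

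**What to change.** For the period-by-period comparison of intervention with control, replace the 120-day rule and the cumulative ratio with two measures from the same refill records:

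1. Proportion of days with TDF-FTC in possession within each of the intervals 0–3, 3–6, 6–9 and 9–12 months.
2. Whether the refill due at the visit closing the interval was obtained, for the closing visits at which a refill is planned (months 3, 6 and 9).

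Keep 120-day discontinuation and re-initiation as descriptive end-of-study summaries.

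Interval measures alone do not remove the lag, so the plan should also state in advance which refill each window can affect. In clusters b and c, possession within the window is largely fixed by the supply prescribed about 2 weeks before exposure, and the effect falls on the refill at the closing visit. For cluster a this depends on the first supply, which should be stated. Cluster d has no later planned refill within follow-up, so refill measures cannot inform its intervention period and self-report must carry it.

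No new data are needed. The cost is that short gaps and variation in visit timing will count as non-possession, so rates will be higher than under the 120-day rule.

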**Secondary outcomes**		
**HIV testing**	Frequency of participants, defined as the number of participants who reported being tested for HIV during the previous three months	3, 6, 9, 12 months
**Sexual and mental health mini-app use**	Frequency of participants, defined as the number of participants who reported using the mini-app in the past three months to receive information about sexual and mental health comparing their pre-intervention and post-intervention engagement	3, 6, 9, 12 months
**PrEP self-efficacy**	Frequency of participants, defined as number of participants who had an increase in PrEP self-efficacy when comparing their pre-intervention and post-intervention self-efficacy	3, 6, 9, 12 months
**HIV incidence**	Frequency of participants, defined as number of participants who reported who have newly diagnosed with HIV in the previous three months	3, 6, 9, 12 months

Secondary outcomes will include HIV testing rate, mHealth use, self-efficacy assessment, and HIV incidence.

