### Data collection activities

In accordance with the demonstration study design, participants in the stepped-wedge design will undergo clinical monitoring for assessment of adherence and side effects every month for the first 3 months after PrEP initiation and every 3 months starting from the 4th month per current US CDC and WHO guidelines, provided by their respective study hospital. All study participants will be required to complete clinical visits at their respective study hospital for PrEP initiation (month 0) as well as for follow-up at months 1, 2, 3, 6, 9 and 12 (Table 1). Baseline survey and follow-up surveys will be administrated through a professional Chinese online survey engine Sojump (Sojump, Shanghai, China) that has been widely used in China-based research studies. Research staff will monitor the survey responses and upload to a secure Dropbox account on a weekly basis.

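### HIV incidence is defined by participants' reports although clinic HIV results are collected and seroconverters leave the study, so infections can be undercounted; the HIV-testing outcome is driven largely by visit attendance

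*Protocol article*

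**What the plan says.** All references are to the protocol article.

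- **HIV incidence** (Table 2, Secondary outcomes) is a count of participants, "defined as number of participants who reported who have newly diagnosed with HIV in the previous three months", at months 3, 6, 9 and 12.
- **Clinic results** (Study measures and outcomes): "Each follow-up at the 3, 6, 9, 12 months will include an online survey and a clinical assessment". On the clinic side, "The clinical assessment will include testing results related to HIV, STIs" among other items.
- **Survey content** (same section): "The online survey will collect data related to number of sexual partners, HIV testing, PrEP uptake" and some further items. HIV testing is named; a new HIV diagnosis is not.
- **Seroconversion** (same section): "If a participant seroconverts to HIV positive, their participation in the study will be terminated".
- **HIV testing** (Table 2, Secondary outcomes) is "defined as the number of participants who reported being tested for HIV during the previous three months", at the same four time points. The source of the test is not restricted.
- **Visits** (Data collection activities): "All study participants will be required to complete clinical visits at their respective study hospital", whatever the condition. Completing clinical follow-ups is how Table 2 measures retention, a primary outcome.
- **Other routes to a test** (Control condition): every participant can request free HIV self-tests through the mini-app.
- **Analysis**: both outcomes are to be modelled in a similar way to the primary outcome.

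**The concern.** The incidence definition rests on what participants say, looking back over a quarter, although a laboratory result is collected at the same time points. It also sits badly with the rule that ends participation on seroconversion. The infections the trial detects itself are the best documented, yet they may have no survey in which to be reported. Incidence in a PrEP cohort would then look lower than it was, and with so few events expected, a handful of missed cases matters.

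For HIV testing, a participant who attends the quarterly assessment has in effect been tested by protocol, in either condition. The outcome then has little room to respond to the intervention, and an apparent gain in testing could simply restate better retention.

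**Working it through.** The article gives no expected number of infections and no expected testing proportion, so there is no planned figure to reproduce. The check compares the sections and then sizes the two effects under stated assumptions.

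**1. Which infections can be reported?**

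| How the infection comes to light | Can it enter the count as defined? |
|---|---|
| Study visit at month 3, 6 or 9, survey completed before the result is known | No. Participation ends, so there is no later survey |
| Study visit at month 12, survey completed before the result is known | No. There is no later survey, even without the termination rule |
| Any of these visits, survey completed after the result is known | Yes, if the survey asks about it and the participant reports it |
| Outside diagnosis between visits | Yes, if a survey is still completed before participation ends |

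The article pairs a survey with an assessment at each follow-up but does not give their order, so rows 1 and 2 cannot be told apart from row 3.

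**2. Size for incidence.** Inputs: 700 participants and 12 months of follow-up (Sample size; Study design and rationale). The incidence rate and the share captured by report are my assumptions.

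- Maximum person-time = 700 × 1 year = 700 person-years. Loss to follow-up lowers it.
- Expected infections = 700 × rate / 100. Counted infections = expected × share captured.

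| Assumed rate per 100 person-years | Expected | Counted at 0% | Counted at 25% | Counted at 50% |
|---|---|---|---|---|
| 0.5 | 3.5 | 0 | 0.9 | 1.8 |
| 1 | 7 | 0 | 1.8 | 3.5 |
| 2 | 14 | 0 | 3.5 | 7 |
| 3 | 21 | 0 | 5.3 | 10.5 |

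**3. Size for HIV testing.** Let *a* be the share attending the quarterly assessment and *s* the share of non-attenders tested elsewhere, both assumed. Taking attenders as tested:

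proportion tested = *a* + (1 − *a*) × *s*

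| *a* | *s* = 0 | *s* = 0.25 | *s* = 0.50 |
|---|---|---|---|
| 0.80 | 0.80 | 0.85 | 0.90 |
| 0.90 | 0.90 | 0.925 | 0.95 |
| 1.00 | 1.00 | 1.00 | 1.00 |

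With *a* = 0.80, doubling outside testing among non-attenders from 0.25 to 0.50 moves the outcome by 0.90 − 0.85 = 0.05. With *s* = 0.25, raising attendance from 0.80 to 0.90 moves it by 0.925 − 0.85 = 0.075 with no change in testing behaviour. The outcome equals attendance only if *s* = 0.

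**The case against.** **Clinic results may be what was meant.** The incidence wording is awkward and names no survey, the listed survey items include no new diagnosis, and the only source of HIV status named is the clinical assessment. Loose drafting in a condensed article is plausible. But the text says participants reported, and the same table names refill records where it intends records (possession ratio, discontinuation, reinitiation). The wording needs correcting on either reading.

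**Loss of events is not shown.** A reader might infer that every infection found by the trial is missed. The documents do not support that: the order of survey and result is unstated, and outside diagnoses made before a survey can be reported. This objection stands, and the claim is limited to a possible undercount.

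**Few events in any case.** With 3.5 to 21 expected infections in four clusters, a model comparison says little however cases are found. That is true, but it does not excuse a definition that can lower the reported rate.

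**HIV testing is not just attendance.** A reader might infer that this outcome only re-measures visits, or that participants are tested at all six follow-up visits. Neither is supported. Outside tests and mini-app self-tests count, and the online survey can be answered without attending. HIV results are stated for months 3, 6, 9 and 12 only; the early monthly visits are described in terms of adherence and side effects. Pill counts may be done by phone, so a completed follow-up need not always include an on-site test. The survey item itself is not shown and may already separate study tests from others. What remains is overlap with retention and a ceiling among attenders.

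**Conclusion.** The incidence point holds. Followed literally, the definition can miss infections detected at study visits, while a better source is collected at the same four time points. How many would be missed cannot be determined from the article; the illustrative counts rest on assumed rates and capture shares and on full follow-up.

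If under-reporting were equal in the two conditions, the main harm would be a rate that is too low and fewer events to compare. A reader might infer that it differs by condition, because the community organisations both deliver the intervention and collect the surveys. The documents do not show this, and they describe the surveys as self-administered.

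The HIV-testing point is secondary and concerns interpretation: the outcome is driven mainly by attendance and is near its ceiling among attenders, but is not identical to attendance.

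Both outcomes are secondary. The primary analysis and sample size are unaffected, and the rule that ends participation on seroconversion is not in question here.

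**What to change.** **HIV incidence.** Define an incident infection as the first positive HIV result at a clinical assessment, plus documented outside diagnoses. Count it at the visit where it is detected, before participation ends, with person-time running from PrEP initiation. Survey reports can serve as a prompt to obtain documentation. The Analysis section treats all secondary outcomes as binary, so it should say how the person-time rate is reported alongside. The cost is a change of wording, since the results are already collected, plus linking each result to the participant's cluster.

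**HIV testing.** State that the outcome includes tests done at study assessments and interpret it next to retention. If the survey data already distinguish study tests from others, restrict it to tests outside scheduled visits, including mini-app self-tests. Trial status says recruitment has begun. Rewording the survey item now has a price: in a stepped-wedge trial, a change in measurement over calendar time is entangled with the rollout. If the data do not allow the split, careful interpretation or dropping the outcome is cheaper than a mid-trial change.
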